### Participants and setting

Participants will be recruited through residential aged-care facilities. Residential aged-care facilities within Australia are government-funded organisations that provide additional support for families who may have a family member with dementia, whereby many move from their residential homes into a residential aged-care facility so that they can be monitored and provided with additional care. PASS^2019^ power analysis and sample size software (ncss.com/software/pass; NCSS, Kaysville, UT, USA) was used to derive the sample size. The Neuropsychiatric Inventory Questionnaire–Nursing Homes (NPI-NH) is the primary outcome measure. Total sample size for a 2 × 2 crossover design assuming a two-sided *t* test to detect a mean difference of 6 on the NPI-NH scale with a standard deviation of 13 (for the difference) is 40 for a power of 80% and significance level of 5%. Fifty participants will be recruited to allow for a 20% attrition rate. Participants will be eligible to participate if they live in a residential aged-care facility, are aged 65 years or older, have a diagnosis of mild dementia (indicated by a score ≥ 20 on the Mini Mental State Examination [MMSE]), are able to speak English, are known as compliant with taking medication, are not bedridden, and are able to provide informed consent. Participants will be excluded if they have certain health conditions, such as frontotemporal or Lewy body dementia; have other comorbidities, such as epilepsy, anorexia nervosa, comorbid psychiatric conditions, Parkinson’s disease, or congestive heart failure; have a history of myocardial infarction or anginal pain, stroke, liver disease, or renal disease; or are taking medications such as primidone, phenobarbital, carbamazepine, rifampicin, rifabutin, troglitazone, *Hypericum perforatum*, and valproic acid that may interact with cannabis metabolism.

The pre-/post-surveys and focus group discussions are an exploratory, qualitative component of this study, and thus a definitive sample size calculation cannot be determined at this stage. We estimate that six focus groups comprising six to eight participants, including two groups of residential care staff, activity staff (care staff who monitor daily activities and social engagement), and family members, will ensure that data saturation has been reached. Written informed consent will be obtained from all participants, including the residential aged-care staff and the next of kin.

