### Randomisation

The randomisation process for this study will be done by creating a random number list using a 1:1 ratio allocation to ensure an equal number of cases in both the placebo group (*n* = 25) and the treatment group (*n* = 25) using Excel software (Microsoft Corp., Redmond, WA, USA). The determination of participant allocation will be completed by the laboratory manager in the drug manufacturing laboratory, with each case being provided a unique identification (ID) number (1–50). The primary researcher, who is responsible for recruitment, will provide the laboratory manager with the participant’s name to be sequentially matched against with the next available ID number. The laboratory will provide the pharmacy with both CBM and placebo in identical bottles labelled with the ID, but the medical practitioner and research team members will not know the order of treatment until the completion of the study. The pharmacist will place the participant’s name on the bottle before distributing the bottles to the aged-care facilities.

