### Data analysis

#### Quantitative

The results of questionnaires completed on behalf of the aged-care staff, participants and family members will be analysed using IBM SPSS Statistics version 25 software (IBM, Armonk, NY, USA). The responses from the aged-care staff will be the main responses considered for analysis. Where available, participants and family responses will be included for secondary analysis. To examine group differences, the participants will be categorised according to their treatment cycle group allocation (group A or group B). Descriptive statistics will be derived. Each variable will be tested for normality. For those variables that meet the normality assumption, two-sided paired and/or independent *t* tests will be used to examine group differences within and between groups. If the normality assumption is violated, then non-parametric tests such as the Wilcoxon signed-rank test will be used. Within-subject differences of the four measurements between the first and second washout periods will be tested using paired *t* tests to ensure that the washout phase is long enough to rule out any carryover effects [51, 52]. All data collection points will be examined using general linear mixed modelling techniques to see if any changes in behaviour, QOL or pain have occurred over the duration of both treatment cycles. The covariates of weight, average dose of medication, and baseline measures will be controlled for in each model, and any interactions will be tested and reported. The proportion of adverse events during the CBM and placebo phases will be tested and reported for each individual. NPI-NH is the primary outcome measure for this study. All other measures (CMAI, QOL-AD, and Abbey Pain Scale) have been included for secondary analysis. The CMAI will be analysed using the reliability change methodology compared with the NPI-NH to allow small changes to be reported [53]. The α-value will be set at 0.05. In the instance where a participant withdraws halfway through a treatment cycle, the information collected prior to withdrawal will be retained in the study because their personal information will have been de-identified. The data management of the information collected will follow standard university procedures, be stored in a locked cabinet for a period of 15 years, be stored on a password-protected computer, and be backed up regularly in a secure format.

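### Open-ended interaction testing at 0.05 in every mixed model, in a trial sized only for the main NPI-NH difference: modifier tests should be few, named and exploratory

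*Protocol article*

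**What the plan says.** The Quantitative part of the Data analysis section plans general linear mixed models over all data collection points for behaviour, quality of life and pain. Each model controls for weight, average dose and baseline measures. The same sentence then adds that "any interactions will be tested and reported". A general statement follows: "The α-value will be set at 0.05". NPI-NH is the primary outcome; CMAI, QOL-AD and the Abbey Pain Scale are secondary. Staff ratings are the main data, and participant and family ratings are a secondary analysis where they exist. The same section also plans paired or independent t tests, or a non-parametric alternative, for group differences.

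The sample size, under Participants and setting, rests on a two-sided t test in a 2 × 2 crossover. Its stated purpose is "to detect a mean difference of 6 on the NPI-NH scale"; the SD used is 13 and refers to the within-person difference. For 80% power at the 5% level, 40 participants are needed in all, and recruitment is raised to 50 to cover a 20% loss. Nothing there allows for an interaction.

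**The concern.** The interaction clause is a stated rule, not a gap. It covers every model, has no boundary, and stands beside a single unadjusted 5% level. Two things follow. Several modifier tests at 0.05 give an appreciable chance that at least one is significant when none is real. And a trial sized for an average effect has little power for differences in that effect, so a significant modifier in this trial would be weak evidence.

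Average dose is the covariate where this matters most. Under Experimental phase and Adverse events and safety protocol, the dose a participant reaches depends on that person's own adverse events, and placebo volume is titrated in a similar way. A chance treatment-by-dose result could be taken for a dose response although dose was not randomised.

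**Working it through.** **Inputs from the article.** Two-sided alpha 0.05; power 80%; planned difference 6; SD of the within-person difference 13; 40 completers, 50 recruited (Participants and setting). Three covariates in each model and four outcomes (Quantitative).

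**Assumptions.** The article does not say which interactions are meant. The narrowest reading that can yield a modifier claim is treatment by each of the three covariates. Tests are first taken as independent.

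**1. The plan's own figure.** The standard error of the mean difference is 13/√n. With a noncentral t on n − 2 degrees of freedom, power is 80.1% at n = 39 and 81.2% at n = 40, the first even number that allows equal sequences. Then 40/(1 − 0.20) = 50. Both stated figures reproduce.

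**2. Chance of at least one false positive**, 1 − 0.95^k for k tests:

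| Set of tests | k | Chance |
|---|---|---|
| NPI-NH, treatment × 3 covariates | 3 | 14% |
| Same, four staff-rated outcomes | 12 | 46% |
| Same, one further reporter throughout | 24 | 71% |
| Same, two further reporters throughout | 36 | 84% |

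With 12 tests, 12 × 0.05 = 0.6 false positives are expected. The chance passes one half at 14 tests (51%).

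The four outcomes are probably correlated. Simulating the 12 tests with an assumed common correlation between outcomes of 0.3, 0.5 or 0.7 gives 44%, 40% and 34%. The last two rows of the table are upper readings, because other reporters' ratings are used only where available.

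**3. Detectable interaction on NPI-NH.** Take the difference in treatment effect between two subgroups of 20, with SD 13 in each:

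- SE = 13 × √(1/20 + 1/20) = 4.11.
- Difference detectable with 80% power, 38 degrees of freedom: (2.02 + 0.85) × 4.11 ≈ 11.8 points.
- Ratio to the planned effect: 11.8/6 = 1.97.
- Power for a 6-point interaction: 30%.

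For a continuous modifier, the detectable slope is about 5.9 points per SD of the modifier. Between one SD below and one SD above its mean, that is again about 11.8 points.

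**4. Sensitivity.**

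| Completers and split | Detectable with 80% power | Power for 6 points |
|---|---|---|
| 40, 50/50 | 11.8 | 30% |
| 40, 30/70 | 12.9 | 26% |
| 40, 20/80 | 14.8 | 21% |
| 50, 50/50 | 10.5 | 36% |

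**The case against.** This is a phase II trial with one named primary outcome, and no interaction is given confirmatory status. Reporting every interaction tested shows readers the denominator and guards against selective reporting. Low power for interactions is common to all trials sized for a main effect. The covariates are continuous and no subgroup split is planned. The models use repeated measurements, adjust for baseline and keep data from participants who withdraw, so SD 13 may not describe their precision exactly. An analysis plan, not shown, could list the interactions.

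Much of this stands, and it limits the point. The split in the calculation is only illustrative, and the test counts are assumptions. It does not remove the point: full reporting changes neither the error rate nor the power, and a later analysis plan would have to narrow a rule that the article already states.

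Three stronger readings are tempting and are not supported:

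- *A false modifier finding is likely.* On the narrowest reading the figure is 14% for NPI-NH and at most about even odds (46%) over four outcomes. One could count all 10 two-way interactions among treatment, time and the three covariates, but six of the 10 do not involve treatment and cannot produce a modifier claim. A seventh, treatment by time, is arguably a core question in a repeated-measures model.
- *The primary NPI-NH estimate will depend on which interactions are kept.* The article says that interactions are tested and reported, not that they stay in the model. The planned t tests contain no interactions, and the article does not say that the NPI-NH conclusion comes from a model that does.
- *The treatment coefficient will become the effect at zero weight or zero dose.* That requires retained interactions and uncentred covariates, and the article states neither.

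**Conclusion.** The point holds as a cheap improvement, not as a flaw in the primary analysis. The rule as written invites modifier findings that 40 completers cannot support. The chance of at least one false positive is about 14% for NPI-NH and up to about 46% over four outcomes, if the tests are treatment by three covariates and independent. Correlated outcomes lower it, to about 34% to 44% at the assumed correlations; further interactions or reporters raise it. A true modifier would need to be about twice the planned effect to be found with 80% power, given 40 completers, an even split (or the equivalent contrast on a continuous modifier) and SD 13 throughout. With 50 completers the ratio is 10.5/6 = 1.75.

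**What to change.** Replace the interaction clause with two rules:

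1. The conclusion on the treatment effect for NPI-NH is taken from the analysis without covariate interactions.
2. A short list of treatment-by-covariate interactions is named before unblinding, with covariates centred. Each is reported as an estimate with its 95% confidence interval, together with the number tested, labelled exploratory and without a significance claim.

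Which interactions go on the list is the investigators' choice. Treatment by baseline NPI-NH is one candidate, since the entry criteria under Participants and setting require no minimum symptom level, but nothing in the article makes it the only right one.

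The change affects analysis wording only: no data collection, visit or sample size changes. The small downside is that the trial gives up any confirmatory claim about effect modifiers, a claim it has little power to support in any case.

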### Aims

The primary aim of the present study will be to see if a purified CBM oil is safe and improves behavioural and neuropsychiatric symptoms of dementia (BPSD). In addition, two secondary aims of this study will include examining QOL and discomfort caused by pain among patients with dementia receiving CBM oil.

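### Safety is part of the primary aim, but the only stated adverse event analysis is a difference test at 0.05 in a trial sized on NPI-NH, which cannot by itself support a conclusion of safety

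*Protocol article*

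**What the plan says.** The Aims section puts safety first: "The primary aim of the present study will be to see if a purified CBM oil is safe", followed by improvement in behavioural and neuropsychiatric symptoms. The abstract's aim also names safety.

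The Quantitative part of Data analysis names one primary measure, an efficacy scale: "NPI-NH is the primary outcome measure for this study". On adverse events it says: "The proportion of adverse events during the CBM and placebo phases will be tested and reported". The sentence ends by saying that this is done for each individual. It names no test, interval or margin. The same section adds: "The α-value will be set at 0.05".

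Participants and setting sizes the trial for a two-sided t test in a 2 × 2 crossover and gives the number needed: "to detect a mean difference of 6 on the NPI-NH scale with a standard deviation of 13 (for the difference) is 40". Power is put at 80%, with a 5% level. Recruitment is raised to 50 for 20% attrition. No expected adverse event rate is given for either phase.

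The article also describes safety data that carry no stated between-phase safety analysis: symptom records at dose increases and on the last day of treatment, heart rate and blood pressure, weight and body composition, and a nurse-led review two days into each washout.

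**The concern.** The question asked is whether the product is safe. The stated inferential step asks something else: whether there is significant evidence that event proportions differ between phases. Rejecting the null in the adverse direction answers the first question unfavourably. Failing to reject does not answer it favourably, because a small trial can fail to reject when the excess is substantial.

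The article offers no other criterion for the safety half of its primary aim. It therefore leaves room for a non-significant comparison to be read as reassurance when the data are still compatible with a sizeable excess of events. That misreading would favour the product, in residents whose frailty and comorbidity the Discussion itself stresses.

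**Working it through.** **1. The plan's own figure.** Inputs from Participants and setting: difference 6, SD of the difference 13, two-sided 5%, power 80%.

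- Normal approximation: n = (13 × (1.960 + 0.842) / 6)² = 36.8, so 37.
- Noncentral t: 39 participants give power 80.2% (80.15% with n − 2 degrees of freedom). The next even number, for two equal sequences, is 40, with power 81.2%.
- Attrition: 40 / (1 − 0.20) = 50.

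Both stated figures reproduce. The sizing is sound, but for NPI-NH only.

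**2. What the adverse event test could detect.** The article gives no event rates, no within-person correlation and no named test, so the following are assumptions:

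- one binary outcome per participant per phase (any adverse event);
- a two-sided 5% McNemar test;
- placebo proportion p₀, CBM proportion p₁ and within-person correlation ρ.

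The probability of an event in both phases is p₁₁ = p₀p₁ + ρ√[p₀(1 − p₀)p₁(1 − p₁)]. The discordant probabilities are p₁ − p₁₁ (CBM only) and p₀ − p₁₁ (placebo only). Power is summed over all possible numbers of discordant pairs.

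For 20% v 40% with ρ = 0, p₁₁ = 0.08, so CBM only is 0.32 and placebo only is 0.12. Among 40 participants that is 12.8 against 4.8 expected discordant pairs. A 13 v 5 split of 18 pairs has exact p = 2 × 12,616 / 262,144 = 0.096, and 14 v 4 has p = 2 × 4,048 / 262,144 = 0.031. The typical result therefore falls just short of significance.

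Miss rate (1 − power) for 20% v 40%:

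| n | test | ρ = 0 | ρ = 0.2 | ρ = 0.3 | ρ = 0.5 |
|---|---|---|---|---|---|
| 40 | exact | 59.6% | 52.1% | 47.0% | 30.6% |
| 40 | chi-square | 50.4% | 42.8% | 37.5% | 20.1% |
| 50 | exact | 50.2% | 39.9% | 33.9% | 17.6% |
| 50 | chi-square | 40.1% | 31.2% | 25.9% | 11.5% |

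Exact miss rates at n = 40 for other assumed rates, ρ from 0 to 0.3:

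- 10% v 20%: 82 to 85%
- 10% v 25%: 59 to 69%
- 30% v 50%: 52 to 65%
- 20% v 50%: 11 to 26%

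**3. What an interval would show.** Suppose 20% have an event in each phase and n = 40. The discordant probability is 2 × 0.2 × 0.8 × (1 − ρ), which is 0.32 at ρ = 0 and 0.224 at ρ = 0.3. The 95% half-width is 1.96√(0.32/40) = 17.5 points, or 1.96√(0.224/40) = 14.7 points. An observed difference of exactly zero would therefore still be compatible with an excess of about 15 to 18 points.

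**The case against.** Four points deserve weight.

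- **A reader might infer that safety is assessed only by a significance test.** The article does not support that. Proportions are to be reported as well as tested, descriptive statistics are planned, and vital signs, body composition and washout reviews are collected. What stands is narrower: the test is the only stated analysis of adverse events.
- **A reader might infer that the trial will declare the product safe if the test is non-significant.** No sentence says so. The article is silent on how such a result would be read. This is a risk of misreading, not a planned one.
- **A reader might infer that a large harm would be missed about half the time.** That figure belongs to one assumed case, 20% v 40% with low correlation and about 40 evaluable. It moves widely with the assumptions. The reference to each individual also leaves the planned outcome unclear: if a per-person proportion of records or symptoms is compared, the McNemar figures do not apply. The checklist includes mild items such as dry mouth, so a doubling of any event need not be a large harm.
- **A condensed article may leave safety detail to a full protocol or SAP, and sizing a phase II trial on its efficacy measure is ordinary.** Both are true, and the sizing is not criticised here. But the article does not leave the adverse event analysis open. It chooses a test, and that choice does not match the primary question. The mismatch remains whichever form the test takes.

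**Conclusion.** The point holds as a mismatch between the aim and the analysis. Safety is in the primary aim, the one stated adverse event analysis is a difference test at 0.05, and the trial is sized on NPI-NH alone. A non-significant result would be weak evidence of safety, and nothing in the article guards against reading it otherwise.

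The size of the weakness is conditional on assumed rates, one binary outcome per phase and a paired test. With 40 evaluable, the central case of 20% v 40% is missed 47 to 60% of the time by the exact test (38 to 50% by chi-square) at correlation 0 to 0.3. At correlation 0.5 the figures are 31% (20%). Other assumed rates at correlation 0 to 0.3 span about 11% to 85%. Most of these cases, though not all, exceed the 20% miss rate accepted for NPI-NH. The NPI-NH sample size is correct, and its 80% power is already tied to that scale. This should be changed, but it does not invalidate the design.

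**What to change.** In the Quantitative part of Data analysis, replace the adverse event sentence with wording such as: *For participants with any adverse event, and separately for those with any moderate or severe event, the paired CBM-minus-placebo risk difference will be reported with its 95% confidence interval. The safety conclusion will be based on that interval. A non-significant difference will not be taken as evidence of safety.*

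The moderate and severe grades are already defined in the adverse events protocol and captured on the Appendix form, so no new data are needed and no clinical procedure changes. The cost is two or three sentences and one interval calculation per outcome. The downside is a more cautious safety conclusion, because at this size the interval will exclude only large excesses. The interval does not by itself define an acceptable excess. It shows what the data can and cannot rule out.

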#### Qualitative

NVivo 12 software (QSR International, Doncaster, Australia) will be used for qualitative data management and assistance in the analysis of both the pre- and post-surveys and in the focus groups. Qualitative content analysis will be used to analyse the surveys to assess similarities and differences between responses. The focus group results will be transcribed verbatim, and the transcripts will be thematically analysed by repeated readings and a subsequent open coding process followed by line-by-line coding to identify key themes. To avoid bias, a triangulated approach including reflectivity by the primary researcher during the interview process, member checking to establish confirmability, and verbatim quotes to establish credibility will be used. The primary researcher and the research team at the University of Notre Dame Australia will have access only to the final data set. The data will be stored in university computers on a locked storage drive.

## Discussion

To our knowledge, this is one of the first trials within Australia to evaluate the use of a purified CBM oil at the individual level among those with dementia to examine behavioural effects, QOL, and pain and discomfort. Only a handful of crossover trials have been conducted [14, 16, 41, 42, 54], although the majority have used fixed doses and have not incorporated an individually tailored dosing regimen. Soto et al. [28] reviewed 18 randomised clinical trials examining drugs prescribed for agitation and aggression and found large variations not only in the chosen questionnaires to measure these symptoms but also in the inclusion criteria. On the basis of their results, Soto et al. [28] suggested that trials lasting 9–12 weeks were adequate for assessing an acute response, whereas longer trials (6–12 months) were effective for assessing the stability of a response. The 18-week duration of this study is appropriate to assess the initial dose response [28], and the trial design is also reflective of other protocols of crossover studies and includes two 2-week washout periods to ensure patient safety and a chance for the medication to metabolise out of the body. For example, Babalonis et al. [31] designed a protocol to examine the use of a THC:CBD oromucosal spray among post-stroke spasticity patients and included two 4-week treatment cycles with a 2-week washout period between both cycles.

There are a number of strengths of our study. First, all participants will have a medical diagnosis of dementia. This ensures that the diagnosis is in line with the criteria of the *Diagnostic and Statistical Manual of Mental Disorders, Fifth Edition* [55]. Second, the residential aged-care staff spend a large amount of time with the participants, so they will be able to observe small changes, leading to accuracy in recording of the results. When possible, these results will also be compared with information from the participants and their next of kin to examine similarities and differences. Beattie et al. [56] published a protocol paper outlining a national project to collect multiple QOL perspectives from the care staff, family members and those living with dementia. Comparisons between care staff, family members and self-report QOL scores showed a linear relationship between reporters, with the residents often rating their QOL higher than the care staff [57, 58].

As an additional precautionary step, two separate questionnaires assessing behavioural symptoms have been included to ensure that the smallest effects of CBM oil are observed. A strict safety protocol monitoring of adverse events and nurse-led reviews during the washout periods will also be followed to ensure participant safety, which has been included due to the average age of the participants, additional medications currently prescribed, and the likelihood of having a comorbid condition. Weier and Hall [15] suggested that the therapeutic benefits of CBM are observed among patients with dementia when administered alongside adjacent therapy or medication. In addition, the dose of medication will be titrated to ensure that each participant receives their best tolerated dose and minimises the onset of any adverse events. This process of ‘start low and go slow’ is reflective of other studies as well as government documentation from Queensland Health [59, 60]. Educational training with the aged-care staff will be completed before the first participant is recruited to prevent unexpected issues arising during the trial and to ensure that they are familiar with the structure of the overall research protocol as well as the questionnaires.

This study has used a holistic approach to gain more in-depth information about BPSD and to capture staff and family members’ perceptions of CBM. The inclusion of the qualitative phase is important because little research has been completed to gain understanding of personal views of CBM use and the effects thereof in this setting. This approach allows the researchers to understand the perceived strengths and challenges in the use of cannabis within an institutional setting. Many symptoms associated with dementia, such as wandering, agitation, aggression, and psychotic behaviours, contribute to fatigue and burnout experienced by many caregivers [61]. Feast et al. [62] reviewed the relationship of BPSD and well-being of informal caregivers (child-adult or spousal caregivers) and found that the most distressing symptoms for caregivers were depressive behaviours, agitation and aggression, apathy (including irritability), aberrant motor behaviours, and delusions.

A number of challenges have been identified in the proposed study. It may be difficult to find those with a dementia diagnosis who have the cognitive capacity to give informed consent, because many experience a loss of short-term memory, intellectual reasoning, rationality, and social skills [1, 2]. This may lead to difficulty in recruiting participants into the trial and excluding those who do not have the capacity to give informed consent; yet, they are potentially the ones who exhibit a greater number of behavioural occurrences. Those who experience mild to moderate dementia still exhibit symptoms such as depression and anxiety and both verbal and physical agitation [2]. However, due to the limited legislation regarding including those who do not have the cognitive capacity to give informed consent in research projects, this limits who can be included in this study. The replication of this study design to include those with a moderate to severe diagnosis would warrant further generalisability of the results. Irreversible progression of cognitive impairment, the associated complications and comorbidities, and frailty of the participants may lead to participants dropping out of the study. To accommodate this, we have included a 20% increase in the sample size. It is also difficult to know if the questionnaires chosen for this study are suitable and sensitive enough to measure the changes attributed to the use of CBM oil, because no ‘gold standard’ exists to measure BPSD. Therefore, both the NPI-NH and the CMAI have been selected to account for the small effects. The pharmacodynamics of the medication will be monitored during the treatment cycles through the use of non-invasive body composition measures and monitoring of heart rate, blood pressure and weight. These measures will be collected by a research nurse external to the aged-care facilities to improve the feasibility of the study, to avoid additional workloads placed on the aged-care staff, and to ensure that each participant is receiving their best tolerated dose. In addition, only one residential staff member has been selected to complete the questionnaires, because they spend a great deal of time with the residents and can report symptoms easily. Independent reviews have not been selected for this study, because they are unfamiliar to the participants, which may lead to inaccuracy in recording of the results.

